### Storage of biological specimens for molecular analysis/future use

One labeled urine and one vaginal sample will be stored in phosphate-buffered saline at minus 80 degrees for four years in a research biobank associated with DH. After this period, the samples will be destroyed.

#### Adverse event reporting and harms

Minimal risk to the participants is anticipated. Some participants may feel reluctant or anxious about self-collecting samples; therefore, RAs are trained to provide instructions using a laminated guide card. Enquiring about sensitive topics like anxiety, depression, and DV may cause emotional distress. To address this, all participants are offered contact information for available support services. Participants who express suicidal ideation are referred to the psychiatry department at DH.

All adverse events are recorded and reviewed during weekly audit meetings, and an appropriate plan of action will be developed.

#### Auditing trial conduct

Trial conduct is reviewed during weekly audit meetings. However, an informal audit by an independent researcher halfway through the trial completion was conducted which was not planned initially.

### Ethical considerations and post-trial care

Prior to the start of participant inclusion, ethical approvals were obtained from the Nepal Health Research Council (NHRC), the Institutional Review Committee of Kathmandu University School of Medical Sciences (IRC-KUSMS), and the Regional Committees for Medical and Health Research Ethics (REK). Any significant amendments to the protocol, such as the addition of an extra test for *Tv* after enrollment of the first half of the participants, are implemented only after obtaining approval from the same ethical committees.

In the case of positive *Ng* results, a new cervical swab will be collected by a health practitioner for culture and AMR testing. Treatment will be adjusted accordingly based on the results.

### Access to full protocol, participant-level data, and statistical code

In line with institutional policy and funding body requirements, all research data, including metadata, will be made accessible through a national data repository (SIKT) once the data has been anonymized. Depending on academic journal requirements, the study protocol and datasets may also be made available at an earlier stage when publishing.

### Dissemination plan

We plan to publish six articles in peer-reviewed journals as per the sequence of authorship. We plan to disseminate the study results in the year 2027. Research findings will be presented at national and international conferences.

## Discussion

A syndromic management approach has long been the standard of care for women presenting with bothersome VD in LLMICs. Compared to etiological-based diagnosis, syndromic management offers advantages in affordability and applicability during the initial visit to a health facility, thereby allowing broader population coverage and helping to limit the spread of infections [15, 42]. However, its major drawback is the overtreatment with antibiotics, particularly due to poor accuracy in detecting cervical infections caused by *Ct* and *Ng*. Given the global concern about AMR, optimizing the use of antibiotics has become imperative [14].

Over the past decade, several POCTs have been developed for STIs, enabling rapid, etiological diagnosis and potentially improving STI care and prevention. Despite a WHO “call for action,” the implementation of POCTs for STI management in LLMICs has not been widely realized [14, 16].

To examine whether implementing POCTs for STIs, striking a balance between accuracy and affordability, can reduce antibiotic use, this pragmatic RCT compares a combination of POCTs with standard syndromic management in the treatment of abnormal VD. However, implementing POCTs in LLMICs faces numerous barriers beyond cost. One important barrier may be limited knowledge among women and health practitioners about VD and appropriate antibiotic use, which could hinder the acceptability and uptake of POCT-based care.

Additionally, previous studies have shown that women experiencing common mental health disorders or DV may present with somatic symptoms such as VD [3, 32–34]. Therefore, this study also explores the impact of providing education and addressing psychosocial issues on over-the-counter antibiotic purchases, symptom progression, and patient satisfaction. Implementation studies such as POCT-BRA are important for addressing these challenges and can help bridge the gap in adapting POCTs to routine healthcare systems. This study evaluates the effectiveness of combining POCTs for STIs in relation to a globally significant and real-world outcome: antibiotic overuse.

A limitation of the trial is that the POCT used for *Ct* and *N*g is currently too expensive to be widely implemented in LLMICS. This POCT serves as a proxy for similar, highly accurate tests that may become more affordable over time, particularly if demand and market competition increase. Furthermore, the trial does not include fungal infections, as they generally do not lead to severe complications. However, fungal infections may account for a proportion of cases of bothersome VD in women without any STI.

## Trial status

Recruitment began on April 22, 2024. Inclusion of 1500 participants was completed on September 25, 2025. Follow-up of the participants is scheduled to be completed by December 31, 2025.

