**Methods:**

This study is a randomized controlled double-blind, superiority trial with follow-up assessments at 4 weeks and 4 months conducted in a Nepalese teaching hospital and its outreach centers. Participants are randomly assigned to one of three study arms: Arm 1 receives treatment, based on syndromic management; Arm 2 receives POCT-guided treatment using the *Cepheid GeneXpert®* (for *Ct* and *Ng*), pH and whiff tests (for BV and *Tv*), and the *OSOM®* test (for *Tv*); Arm 3 receives the same POCT-guided treatment as Arm 2, plus an educational intervention, and referral for psychosocial concerns. The primary outcome is the proportion of participants overtreated with antibiotics at the primary consultation, comparing Arm 1 versus Arms 2 and 3. Secondary outcomes include over-the-counter antibiotic acquisition, subsequent health-seeking behavior, and changes in VD symptom development over time.

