### Sample size

Based on the study objectives, recruitment feasibility, and the desired precision of estimates (i.e., two-sided 95% confidence intervals [CIs]), the sample size was calculated using PASS Sample Size software. Antibiotic use will be compared between both Arm 2 and Arm 3 versus Arm 1 (*N* = 1500) at the first consultation and will serve as a secondary outcome. The effect of the educational measures on the use of OTC antibiotics will be compared between Arm 2 and Arm 3 (*n* = 1000) at 4 weeks and 4 months of follow-up.

It is estimated that approximately 85% of women in LLMICs are over-treated with antibiotics for VD, and around 50% receive antibiotics that contribute to AMR. Furthermore, about 40% of women are expected to purchase antibiotics OTC. The overtreatment with antibiotics and the use of AMR will be assessed at the first consultation whilst the adherence to the treatment recommendation will be assessed at 4 weeks as primary outcome and at 4 weeks and 4 months of follow-up as secondary outcome.

With 1500 participants randomized equally across the three arms (allocation ratio of 1:1:1), a 10–20 percentage point difference between groups in any of these measures will produce CIs with a width of 8–12%, achieving at least 90% power for each comparison at a significance level of 0.017 (adjusted from 0.05 to account for multiplicity with three primary outcome measures). For the assessment of over-the-counter antibiotic use, even with a 40% loss to follow-up, the expected CI width remains around 15%.

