#### Baseline data and secondary outcomes

Baseline data are collected using a C-ACASI with RAs available to assist. This ensures the inclusion of participants with limited literacy. Data are uploaded to a secure cloud and later transferred to the CRF. These data are acquired as follows:

Questions adapted from: WHO clinical study guidance on POCT for VD to establish sociodemographic profile, reproductive and sexual history, and the VD symptoms [41].The Hopkin’s Symptom Checklist for screening anxiety and depression [37, 38].DV screening questions adapted from the 2016 Nepal Demographic Health Survey, which have been validated in Nepali [39].Health practitioners’ documentation of clinical findings on paper questionnaires, which are collected and transferred to the CRF [41].

Secondary outcome data are collected during telephone follow-ups at one- and four-month post-consultation. These follow-ups are conducted using printed questionnaires by RAs who are blinded to group assignments. The information is later entered into the CRF by a researcher.

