### Statistical analysis

Descriptive analysis will be used for demographic characteristics, reproductive history, questions related to VD, clinical findings, working diagnosis by health practitioners, microbiological results, anxiety and depression scores, prevalence of DV, and prescription of medications (including antibiotics). At follow-up, we will describe symptom development, treatment adherence, and patient satisfaction for all participants after one and four months. Anxiety and depression scores will be assessed for the remaining participants at the four-month follow-up, after recruitment is completed, due to time constraints. The expected sample size is approximately 400 participants.

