### Protocol non-adherence and missing data

Protocol non-adherence is defined as participants in the intervention arms (arms 2 and 3) receiving antibiotics to treat *Ct*, *Ng*, *Tv,* or BV despite negative POCT results. These cases will be described in groups according to the three antibiotic treatment categories used: (a) treatment for *Ct*, (b) treatment for *Ng,* and (c) treatment for *Tv* and BV.

The proportion of missing data will be reported, and efforts will be made to determine the reason for missingness. The primary analyses will be complete case analyses. Two of the primary endpoints are registered immediately after the intervention and will not be subject to any substantial missingness. The third primary outcome is recorded at 4 weeks post-intervention and may have a greater risk of missingness. Multiple imputation methods will be considered if this missingness exceeds 20%.

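### The stated close of follow-up, 31 December 2025, falls 15 to 25 days before the last participant's 4-month contact is due

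*Protocol article*

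**What the plan says.** The Trial status section gives three dates: "Recruitment began on April 22, 2024"; "Inclusion of 1500 participants was completed on September 25, 2025"; and "Follow-up of the participants is scheduled to be completed by December 31, 2025".

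The follow-up schedule appears in several places:

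- The abstract (Methods) describes "follow-up assessments at 4 weeks and 4 months".
- Baseline data and secondary outcomes: "Secondary outcome data are collected during telephone follow-ups at one- and four-month post-consultation".
- Sample size: the effect of the educational measures on over-the-counter (OTC) antibiotic use "will be compared between Arm 2 and Arm 3 (*n* = 1000) at 4 weeks and 4 months of follow-up". Adherence at 4 months is also listed there as a secondary outcome.
- Statistical analysis: symptom development, adherence and satisfaction are to be described for every participant at both time points. Anxiety and depression scores at 4 months are limited to those still to be contacted once recruitment has ended. For these, "The expected sample size is approximately 400 participants".

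The third primary outcome, adherence, is taken earlier: "The third primary outcome is recorded at 4 weeks post-intervention" (Protocol non-adherence and missing data). The other two primary outcomes are recorded at the first consultation. Retention and follow-up allows up to four telephone attempts at each time point.

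**The concern.** The dates and the schedule cannot both be met. A woman included on 25 September 2025 has not reached 4 months by 31 December 2025, and no section gives a contact window, shortens follow-up for late enrollees, or limits the closing date to the 4-week call. The protocol version is dated 30 October 2025, after the last inclusion, so that inclusion date was known when the closing date was stated.

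If the closing date governs the work, the last enrollees are either called before 4 months or have no 4-month record. OTC purchases and adherence concern behavior up to the call, so a call at just over 3 months covers a shorter period than one at 4 months. On the calendar-month reading, women enrolled at the very end of August reach 4 months on or just before the closing date, which leaves little or no time for repeat attempts.

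**Working it through.** **Inputs from the article.** Recruitment from 22 April 2024 to 25 September 2025; 1500 included; close of follow-up 31 December 2025; contacts at 4 weeks (also called one month) and 4 months after consultation.

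**Assumption, not in the article.** Uniform accrual. The article gives no monthly enrolment.

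**1. Time available to the last participant.** 25 September to 31 December 2025 = 5 + 31 + 30 + 31 = 97 days. That is 97/7 = 13.9 weeks, or 97/30.44 = 3.2 months.

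**2. When the last 4-month contact falls due.** Due date = 25 September 2025 + length of follow-up. Latest enrolment date = 31 December 2025 − length of follow-up.

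| Meaning of 4 months | Days | Last contact due | Days after the stated close | Latest enrolment that fits |
|---|---|---|---|---|
| 16 weeks | 112 | 15 January 2026 | 112 − 97 = 15 | 10 September 2025 |
| 17 weeks | 119 | 22 January 2026 | 22 | 3 September 2025 |
| 120 days | 120 | 23 January 2026 | 23 | 2 September 2025 |
| Calendar months | 122 | 25 January 2026 | 25 | 31 August 2025 |

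The stated closing date is not reproduced under any of these readings. The 16-week reading is included because the article uses 4 weeks and one month interchangeably.

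**3. How many women this touches (estimate).** Recruitment lasted 522 days counting both ends, so mean accrual is 1500/522 = 2.874 per day. Number affected = days after the stated close × daily accrual.

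- 16 weeks: 15 × 2.874 = 43 women, 43/1500 = 2.9%.
- Calendar months: 25 × 2.874 = 72 women, 72/1500 = 4.8%. About two thirds, 48, would be in Arms 2 and 3.
- If September accrual ran at half to twice the average, the calendar-month count is 36 to 144. The 16-week count is then 22 to 86.

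**4. Primary outcomes.** The last 4-week adherence call is due on 25 September + 28 days = 23 October 2025, well before the close. The other two primary outcomes are complete at the consultation.

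**5. The anxiety and depression subset.** Read as calendar-month contacts due after 25 September 2025, this subset is everyone enrolled from 26 May to 25 September 2025, or 123 days. Uniform accrual gives 123 × 2.874 = 353 women before any loss. Those who reach 4 months by 31 December were enrolled from 26 May to 31 August, or 98 days: 98 × 2.874 = 282. The stated figure is about 400. Since 353 is below 400 even before loss, uniform accrual does not reproduce the article's figure. Reaching 400 would need at least 400/123 = 3.25 inclusions per day, 13% above the mean.

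**The case against.** The strongest reply is that this is a trial-status line, not a rule for conduct. It reports a schedule. Nothing says that calls stop or that the data are locked on that day, and the calls may simply be made when due. That stands in part: harm follows only if the date is applied. It does not remove the contradiction, because the article gives a date that its own schedule cannot meet and says nothing on how the last enrollees are handled.

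The impact is also modest. A calendar cut-off treats the randomized arms alike, so it costs completeness and uniform timing and gives no evident bias between arms. The anxiety and depression reassessment is presented under descriptive analysis, not as a comparison between arms. These points stand.

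A reader might infer more than the documents support in three ways:

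- **A fixed loss of about 70 women.** That figure needs both uniform accrual and calendar months. The article states neither, so only a range can be given.
- **A cut of about 20% in the anxiety and depression subset** (from 353 to 282). This rests on the same accrual assumption, which does not reproduce the stated 400, and on one reading of who remains to be assessed. The mismatch may reflect faster late accrual or a different count, so it does not show that 400 is wrong.
- **An addition to a loss of 40% already incurred.** In the Sample size section, 40% is a tolerance scenario for the precision of OTC use. Even on top of it the effect is small. With 300 per arm and 40% OTC use in both, the 95% interval is 2 × 1.96 × √(2 × 0.4 × 0.6/300) = 15.7 points wide. Removing a further 4.8% (300 × 0.952 = 285.6 per arm) gives 16.1 points.

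**Conclusion.** The point holds. The stated close of follow-up is 15 to 25 days too early for the 4-month contact of the last participant; this is date arithmetic and needs no assumption beyond the meaning of 4 months. If the date is applied, women enrolled in roughly the last 15 to 25 days of recruitment would be contacted early or missed. Under uniform accrual that is about 43 to 72 women (3 to 5% of 1500), or about 36 to 144 on the calendar-month reading if September accrual ran at half to twice the average.

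The exposure is confined to 4-month secondary and descriptive data: OTC antibiotics, adherence at 4 months, symptoms, satisfaction, and anxiety and depression scores. None of the three primary outcomes is affected. The date should be corrected because following it would cost data that are cheap to keep, but it does not threaten the trial's main conclusions.

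**What to change.** Move the stated close of follow-up to no earlier than 25 January 2026, plus enough time for the up to four call attempts for the last enrollees. Check that the figure of about 400 for the 4-month anxiety and depression assessment agrees with the actual enrolment dates and the revised close, and restate it only if it does not. If some late contacts have already been made early, report their timing.

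The cost is a few more weeks of telephone calls and a slightly later data lock. The Dissemination plan places the results in 2027, which leaves room for this.

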## Data Availability

The datasets generated during the current study will be available at the SIKT data repository (use link, look for SIKT Data repository), once data is anonymous (e.g., the unique identifier is deleted). Summaries of dataset used for analysis are made available as soon as relevant papers are published.

## Abbreviations

AMR: Antimicrobial resistance
BV: Bacterial vaginosis
C-ACASI: Color-coded Audio Computer-Assisted Self-Interview
CI: Confidence interval
CRF: Case report form
*Ct*: *Chlamydia trachomatis*
DH: Dhulikhel Hospital
DV: Domestic violence
IRC-KUSMS: Institutional Review Committee - Kathmandu University School of Medical Sciences
LLMICs: Low- and-lower-middle-income countries
NAATs: Nucleic acid amplification tests
*Ng*: *Neisseria gonorrhoea*
NHRC: Nepal Health Research Council
OPDs: Outpatient departments
ORCs: Outreach centers
OTC: Over-the-counter
PID: Participant identification
POCTs: Point-of-care tests
RA: Research assistant
REK: Regional Committees for Medical and Health Research Ethics
STIs: Sexually transmitted infections
*Tv*: *Trichomonas vaginalis*
VD: Vaginal discharge
WHO: World Health Organization
